## Abstract

**Introduction::**

Hypertension (systemic arterial hypertension [SAH]) is a systemic condition that affects about 30% of the world population, according to data from the World Health Organization (WHO). Drugs used to control this disease have the potential to induce xerostomia, an oral condition in which the decrease of the salivary flow is observed and whose presence leads to the increase of the index of caries, periodontal disease, loss of the teeth, dysgeusia, difficulty of mastication, dysphagia, bad breath and oral burning and impairment of prothesis installed in the buccal cavity, including retention of removable and total dentures.

**Methods::**

This is a randomized, placebo-controlled, blind clinical protocol that aims to analyze the impact of phobiomodulation (PBM) on salivary glands of patients with antihypertensive drug induced xerostomia. Patients will be divided into 2 groups: G1: older adults with xerostomia induced by antihypertensive drugs and treatment with PBM (n = 30); G2: placebo PBM (n = 30). The irradiation will be made using a diode laser emitting at 808 nm with 100 mW and 40 seconds of exposure per site at the salivary glands. Twenty sites will be irradiated weekly for 4 weeks. Non-stimulated and stimulated salivary flow will be analyzed before and after the treatment.

**Results::**

This protocol will determine the effectiveness of photodynamic therapy regarding the reduction of xerostomia in older adults using antihypertensive drugs.

**Conclusion::**

This protocol will determine the effectiveness of photodynamic therapy regarding the reduction of xerostomia in older adults using antihypertensive drugs.

**Trial registration::**

Clinicaltrials.gov – NCT03632096

## Introduction

1

Systemic arterial hypertension (SAH) is a disease that affects a large percentage of the world population, including in Brazil, and is responsible for 9.4 million deaths worldwide, according to a World Health Organization (WHO) survey. Hypertension affects 30% of the Brazilian adult population, arriving at >50% in the elderly and is present in 5% of children and adolescents in Brazil, according to estimates by the Brazilian Society of Hypertension.^[1,2]^

The most frequent complications in patients with this disease are deficiencies in the function of the salivary glands, which results in a change in the quality and quantity of the saliva produced. Due to the important role that saliva plays in oral health, studies evaluating therapeutic protocols for the control and treatment of this adverse drug effect are very important.^[3]^ The low-intensity laser has been widely studied for the treatment of gland dysfunction, which can happen due to various causes.^[4,5]^

Xerostomia is a quantitative–qualitative alteration of the saliva that results in the sensation of dry mouth. This is one of the most common complaints among patients who use continuous drugs to control chronic systemic diseases, including SAH.^[6]^

This condition has been linked as side effects of several drugs that cause salivary dysfunction, including antihypertensive drugs. Diuretics are responsible for decreasing the amount of circulating intravascular and extracellular fluid in the body, including saliva, whereas anticholinergic drugs act directly on the hypothalamus, reducing salivary production.^[7,8]^ The majority of drugs used to treat this chronic disease are anticholinergics, β blockers, and diuretics, that directly influence the quantity and quality of saliva production.^[9–12]^

Antihypertensive drugs act on central alpha 2 adrenergic receptors and generally cause dry mouth. An important central area for the control of salivary secretion and the effects of alpha 2 adrenoceptor activation is the lateral hypothalamus.^[13]^ Alpha-adrenergic blockers, angiotensin-converting enzyme inhibitors, and angiotensin II receptor antagonists are classes of antihypertensives that are also associated with salivary dysfunction. Alpha-1 antagonists (tyrosine and prazosin) and alpha 2 (clonidine) antagonists are salivary flow-reducing; beta-blockers (atenolol and propranolol) also reduce salivary protein levels.^[13]^

The secretion of salivary glands is controlled primarily by the autonomic nervous system. Parasympathetic stimulation produces abundant amounts of aqueous saliva, while sympathetic stimulation produces more viscous saliva.^[6]^Figure 1 shows the main functions of the saliva.

**Figure 1 F1:**
[figure not shown]
Functions of the saliva.

On the other hand, the xerostomia itself is characterized by low saliva production, but it is not necessarily related to the sensation of dry mouth. Nevertheless, it induces discomfort to the patient, interfering with phonation, chewing, starch digestion (ptyalin and salivary amylase), formation of the bolus, swallowing, dysphagia, dysgeusia, difficulty in adapting total and partial removable dentures, caries index (buffer capacity) and periodontal disease (immunoglobulin protection and self-cleaning), besides being a risk factor for bad breath and oral burning syndrome.^[6,14,15]^

In addition to the dry mouth, xerostomia can cause several conditions, such as difficulty in: swallowing food; speaking; the adaptation of partial or total prosthetics; and is also related to: burning in the mouth; halitosis, and caries.^[4,16–18]^ There are reversible causes, where there was no cellular destruction and possibility of recovery through adequate stimuli, and irreversible causes, when glandular destruction does not allow any form of reversal of the condition. In the first case, there is a decrease in salivary flow, while in the second, salivary loss is definitive.^[18]^

There are few effective methods to stimulate salivary flow, including chewing, use of systemic sialogogues, electrical stimulation, acupuncture, and the use of saliva substitutes. These methods have certain deficiencies or limitations and the most common treatment for these cases is the use of artificial saliva, frequently used and for long periods, and some types can affect the integrity of the dental enamel.

Sorbitol used in some artificial saliva formulas can trigger gastrointestinal symptoms, such as diarrhea, due to its osmotic potential. Systemic sialogogues such as pilocarpine and cevimeline hydrochloride produce pulmonary and cardiovascular side effects and may be contra indicated in certain patients according to their underlying disease.^[7,19]^

Sialometry is the most used clinical method to measure the volume of saliva, consisting of the collection of salivary fluid produced. It is considered hyposalivation when the rate of salivary flow is <1 mL/min at rest or <7 mL/min under-stimulation.^[20,21]^ The volume of secreted saliva under the patient's homeostasis conditions is approximately 1 mL/min, which may represent a volume of about 500 to 1500 mL of saliva per day. This amount and the composition of the secreted saliva can be altered in the function of systemic diseases, drugs for the treatment of chronic diseases and stress.^[21,22]^

One of the possibilities for the treatment of xerostomia is the application of photobiomodulation. Photons are absorbed by cytochromes and porphyrins in the mitochondria of the cell. A temporary release of nitric oxide from the cytochrome c oxidase binding site may occur, resulting in increased transcription and cellular respiration.^[23]^

PBM may represent a minimally invasive treatment tool for xerostomia.^[24,25]^ The likely mechanism of action of PBM is that the energy input (adenosine triphosphate [ATP]) in the acinar cells can increase the production of saliva.

The purpose of this study is present a protocol to evaluate the effect of PBM in patients with antihypertensive drug-induced xerostomia.

## Methods

2

Figure 2 shows the flow of the study.

**Figure 2 F2:**
[figure not shown]
Flow of the study.

### Study design

2.1

This is a randomized clinical trial in which all participants have the same chance of receiving treatment and will be randomly selected by using unencumbered envelopes. Participants will not know which group they belong to and the examiner should be unaware of the purpose of the study.

This research will be performed with patients who respond to the call published on the website of the University of Nove de Julho, which will offer the possibility of treatment for xerostomia in hypertensive patients who use drugs to treat the disease. It is estimated that the sample will be 60 patients. These patients will be divided into 2 groups: a placebo one and the other that will receive the PBM.

### Trial registration

2.2

Trial registration: Clinicaltrials.gov—NCT03632096.

It was first posted and last updated in October 11, 2018.

### Sample size

2.3

It is known from published studies that the salivary volume (primary outcome) presents a normal distribution of probabilities, and with a variation coefficient of around 50%. Meanwhile the literature lacks information on the salivary flow difference between irradiated and non-irradiate subjects. Due to the lack of similar published works, the sample size was calculated using estimated effect size and test power as shown in Figure 3.

**Figure 3 F3:**
[figure not shown]
Statistical power of the hypothesis test as a function of the sample size. Each line was calculated for a different effect size.

For the sample size analysis we assumed a 2-tailed *t* test with significant level of 0.05. Figure 4 shows that, for medium (0.750) and large (1000–1250) effect sizes, a minimum of 30 patients per group is sufficient to control statistical variance, ensuring a test power >0.80.

**Figure 4 F4:**
[figure not shown]
Sites of irradiation: parotid, submandibular, and sublingual salivary gland.

#### Inclusion criteria

2.3.1

Patients over 18 years of age, hypertensive patients taking antihypertensive drugs and those who are associated with xerostomia, will be included, except for any other cause for the condition and provided they sign the free consent form. Patients with a serum level of LDL <160 mg/dL and stage 3 renal disease whose renal function reduced their total capacity by 30% to 60%, but without oral repercussion, may be part of this group.

#### Exclusion criteria

2.3.2

Patients with cancer in the oral region, patients in radiotherapy, patients with Sjögren syndrome, diabetics, patients with stage 4 and 5 renal failure, pregnant women, infants, children under 18 years old, and those with any type of photosensitivity.

### Recruitment and randomization

2.4

Patients who respond to the call published on the website of the University of Nove de Julho, which will offer the possibility of treatment for xerostomia in hypertensive patients who use drugs to treat the disease, will be invited to take part in the study. The 60 individuals will be randomized in 2 groups: Group A (30 individuals submitted to treatment with a PBM) and Group B (30 individuals submitted to simulated PBM). Opaque envelopes will be identified with sequential numbers (1–60) and will contain pieces of paper with the information of the corresponding experimental group (A or B). Blocked randomization will be performed in blocks of 6 patients (10 blocks for both treatments; example of a block: AABABB). All patients will have the same chance among themselves, since the method predicts randomness, noting that the participants do not know which group they belong to.

The allocation sequence will be randomized by blocks of 6 subjects in a ratio of 1:1. Each patient will receive a closed envelope to deliver to the clinician responsible for applying PBM. Patients with envelope A will undergo a placebo treatment, where all protocols of PBM application and collection of saliva will be followed, however, the laser equipment will remain off. Patients with envelope B will be submitted to the PBM protocol.

The ratings will be blind to trial participants and data analysts. As patients seek treatment service, sealed envelopes will be delivered to them. The remaining envelopes will be stored for the next patients who present for treatment.

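### Section 2.4 defines the allocation letters A and B in two opposite ways, so the arms could be swapped if treatment and decoding follow different definitions

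*Protocol article*

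**What the plan says.** All of this stands in section 2.4, Recruitment and randomization, of the protocol article.

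- The first paragraph names the arms: "Group A (30 individuals submitted to treatment with a PBM) and Group B (30 individuals submitted to simulated PBM".
- The same paragraph ties the envelopes to those names. They "will contain pieces of paper with the information of the corresponding experimental group (A or B".
- The second paragraph says how the envelope is used: "Each patient will receive a closed envelope to deliver to the clinician responsible for applying PBM".
- It then gives the operative rule: "Patients with envelope A will undergo a placebo treatment", meaning the full procedure with the device off, and "Patients with envelope B will be submitted to the PBM protocol".
- The third paragraph states the blinding: "The ratings will be blind to trial participants and data analysts".

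**The concern.** The treating clinician acts on the letter in the envelope, and the letter has two opposite meanings one paragraph apart. Blinded analysts would normally work with coded groups and need a key to attach the results to arms. If delivery follows one paragraph and decoding follows the other, the two arms change places in the analysis. Because the planned tests are two-tailed, the swapped result can be statistically significant in the wrong direction, and nothing in the p-value would show it. A larger sample would only make the wrong answer firmer. The primary outcome (sialometry) and every secondary comparison between groups would be affected alike.

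**Working it through.** **1. The two definitions side by side**

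| Place in section 2.4 | A | B |
|---|---|---|
| First paragraph (groups) | PBM | simulated PBM |
| Second paragraph (envelopes) | placebo, laser off | PBM |

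These would be compatible only if the envelope letter and the group letter were separate codes. They are not: the first paragraph says the paper in the envelope states the group.

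**2. Does another section settle it?** No. The abstract uses G1 (PBM) and G2 (placebo), not letters. Section 2.5, Study interventions, describes active and simulated application without letters.

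**3. Is the rest of the allocation scheme sound?** Yes. The example block AABABB has 3 A and 3 B, and 60 / 6 = 10 blocks, as stated.

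**4. Reproducing the plan's power.** Inputs from section 2.3, Sample size: two-tailed t test, significance level 0.05, 30 per group, smallest named effect size d = 0.75. The noncentrality is d × √(30/2) = 0.75 × √15 = 2.905 on 58 degrees of freedom.

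- d = 0.75: power 0.815 (normal approximation 0.828)
- d = 1.00: power 0.968
- d = 1.25: power 0.997

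All exceed the stated 0.80, so the plan's figure reproduces.

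**5. Full swap.** Every patient is analysed under the opposite label. The mean difference becomes -d and the variance is unchanged. At d = 0.75 the expected estimate is -0.75 SD. By symmetry, the two-tailed test is significant in favour of sham with probability 0.815 (0.968 at d = 1.00; 0.997 at d = 1.25). The chance of a significant result in favour of PBM is practically zero.

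**6. Partial mismatch, for illustration only.** Let q be the fraction of patients in each arm who were treated opposite to their analysed label. The documents give no value for q; those below are assumptions.

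- Mean difference: d(1 - 2q)
- Within-group variance after mixing: 1 + q(1 - q)d²
- Effective effect size: the first divided by the square root of the second

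With d = 0.75:

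| q (assumed) | Mean difference | Variance | Effective d | Probability of a significant result favouring PBM |
|---|---|---|---|---|
| 0 | 0.750 | 1.000 | 0.750 | 0.815 |
| 0.10 | 0.600 | 1.051 | 0.585 | 0.606 |
| 0.25 | 0.375 | 1.105 | 0.357 | 0.274 |
| 0.50 | 0 | 1.141 | 0 | 0.025 (and 0.025 favouring sham) |

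Holding the variance at 1 would give 0.628 at 10% and 0.298 at 25%. That is slightly optimistic, because mixing two treatments within an arm adds spread.

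**The case against.** The strongest reply is that this is a slip of the pen in an article that condenses a fuller protocol. The working randomization list, the envelopes and the operator instruction are not shown. If they share one key, no patient is misattributed and the result is untouched. That stands, and it limits the point to a risk.

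Several stronger readings are tempting but not supported.

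- **That a swap has occurred or will occur.** A reader might infer this from the reversal. The article shows two conflicting statements, not what was done.
- **That analysts will decode from the article's text.** Section 2.4 says only that they are blinded. It describes no decoding step and does not say which document holds the key.
- **That the arms will be mixed and the effect diluted.** This needs different patients to be treated under different paragraphs. The text speaks of a single responsible clinician, so dilution is less well grounded than a full swap, and the fractions used to size it are assumptions.
- **That the first paragraph must be right because it names the groups.** Nothing in the article ranks one paragraph above the other.
- **That the trial design is faulty.** The ratio, block size, sample size and power are unaffected. This is an internal contradiction, not a poor design choice.

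What the reply does not remove is the contradiction itself. The article states the key, and does so twice, so this is not a detail left to another document.

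**Conclusion.** The contradiction is real and should be corrected. It concerns an operative rule, namely which letter leads to active treatment, and nothing else in the article resolves it. In the worst case, delivery under one key and decoding under the other, the sign of every group comparison reverses: a true +0.75 SD is reported as -0.75 SD, with probability about 0.815 of significance in favour of sham. This rests on the protocol's own 30 per arm, two-tailed 0.05 level and effect size of 0.75, and on the swap being complete. If one key is used consistently, the effect on the result is nil. The figures for partial mismatch (power about 0.61 at 10% and 0.27 at 25%) show only how sensitive the trial would be and do not predict what will happen.

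**What to change.** 1. Take the single key used in the actual randomization list and make both paragraphs of section 2.4 state it. Do not choose a key from the text: if the envelopes already follow the other one, editing the wording alone could create the swap it is meant to prevent.
2. Check that the envelopes (prepared or already used), the operator instruction and the decoding key all agree with that list. Someone who may know the allocation should do this, so that participants, examiner and analysts stay blind.
3. Optional: record at each session whether the device was on or off, so that treatment as delivered can be compared with the list. Such a record reveals allocation and would have to be kept from blinded staff. It is not needed to resolve the contradiction.

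The cost is a short text correction and one check of the list and envelopes. The 30 per group, 1:1 ratio, 10 blocks of 6 and power of 0.815 at d = 0.75 all stay as they are.

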### Study interventions

2.5

The method consists of the application of low-intensity infrared laser in the 3 pairs of major salivary glands—parotid, submandibular, and sublingual. The parameters used will be: Laser DMC emitting at *λ* = 808 nm, 4 J/site, continuous wave, incidence of the beam perpendicular to the irradiated surface (90°) and in contact with it, resulting in irradiance of 3571 mW/site, distributed in 6 external points in each parotid, 2 external points in each sublingual, and 2 points in each submandibular (internal), totaling 20 points—16 extraoral and 4 intraoral, as shown in Figure 4.

Patients will receive 3 applications of photobiomodulation directly in the region of the 3 pairs of salivary glands already described. The detailed radiometric parameters can be observed in Table 1. The laser applications should obey the following criteria: the skin will be cleaned, the mucosa must be free of saliva, and the laser tip should come into contact with the surface to be irradiated, perpendicularly. The first application will be after the stimulating collection and the following applications will be given once a week for another 2 weeks. Two days after the end of the phototherapy will be done the final collections.

**Table 1 T1:**
[figure not shown]
Radiometric parameters.

The placebo group will be submitted to the simulation of laser application, with the device switched off; because it is an infrared and invisible length, the patient will not be able to perceive that the equipment will be turned off. In the group that receives the PBM, the device will have its timer turned off, to avoid the perception of sound difference.

The first collection of saliva will also be done in 2 steps—unstimulated and stimulated. In the non-stimulated collection, the patient will be instructed to swallow and then lower his/her head and collect in a test tube all the saliva produced during 5 minutes. The stimulated collection will be done in the same way, however, the patient will be instructed to chew a sialogogue (silicone fragment to stimulate salivary production) for 5 minutes. After the PBM sessions (4 sessions), in the following week, the saliva will be collected again in 2 steps, as in the initial collection. The initial and final volumes will be compared to verify if there was an increase in the salivary flow. A biochemical analysis will also be made.

#### Harms

2.5.1

No adverse effects have ever been reported while using photobiomodulation with appropriate parameters.

## Study outcomes

3

### Primary outcome

3.1

The primary outcome is the sialometry. The patient will be instructed to position the head forward and keep the eyes open allowing all saliva to passively pass through the collector tube, resting on the lower lip, for 5 minutes. If saliva does not drain, it will be required to be reserved in the region of the buccal floor or on the back of the tongue (without swallowing or spitting). Then, the patient will be instructed to spit out all saliva accumulated in the collection tube. The amount of saliva and foam will be evaluated and properly recorded. Then the dimethicone (removal of the air bubbles) will be used to obtain the final result. For stimulated sialometry, the patient will be asked to chew the sialogogue for 5 minutes and spit the saliva in the collection tube as it is produced.

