### Statistical analyzes

3.3

The data will be analyzed regarding its distribution using the Shapiro-Wilkins test and then submitted to the appropriate tests to determine the differences between the groups. If the outcome presents data with normal distribution, the *t* test will be used. If the outcome does not present normal data, the Mann–Whitney *U* test will be used. All tests will be 2-tailed and the level of significance adopted will be *α* = 0.05.

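### The primary outcome covers two salivary flows, but the trial is sized for one test and no rule says which flow decides

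*Protocol article*

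**What the plan says.** Section 3.1 (Primary outcome) of the protocol article names a single outcome: "The primary outcome is the sialometry". It describes a passive 5-minute collection and then adds a second measurement under the same heading: "For stimulated sialometry, the patient will be asked to chew the sialogogue for 5 minutes".

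Other sections treat both flows alike:
- Abstract, Methods: "Non-stimulated and stimulated salivary flow will be analyzed before and after the treatment".
- Section 2.5 (Study interventions), on the baseline visit: "The first collection of saliva will also be done in 2 steps—unstimulated and stimulated". The final visit repeats both steps.
- The Introduction gives separate hyposalivation limits, below 1 mL/min at rest and below 7 mL/min under stimulation. The two flows are therefore different quantities, not repeat readings of one.

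The sample size section (2.3) speaks of one variable: "the salivary volume (primary outcome) presents a normal distribution of probabilities". It does not say which flow is meant. It assumes a two-tailed t "test with significant level of 0.05" and concludes that "for medium (0.750) and large (1000–1250) effect sizes, a minimum of 30 patients per group is sufficient" for power above 0.80. The large effect sizes are read here as 1.000 to 1.250.

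Section 3.3 (Statistical analyzes) applies one level throughout: "All tests will be 2-tailed and the level of significance adopted will be" 0.05. It gives no order of testing, combination of the two flows, or rule for what makes the primary result positive.

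**The concern.** Three statements do not fit together: a primary outcome made of two variables, a sample size for one test, and the full 0.05 level for every test. At least three decision rules are compatible with the text:

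1. One flow is primary, but it is not named.
2. A significant difference on either flow is enough.
3. Both flows must differ significantly.

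The rules have different false positive rates and different power. Under the first, the stated level and power both hold, but only if the flow is chosen before the results are known. Under the second, the 5% level fails. Under the third, the stated power fails at the smallest effect size that the sample size section claims to cover. While the rule is open, the flow with the better result could be presented as the primary outcome after the fact, and a reader could not tell.

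**Working it through.** **Inputs from the protocol article.** 30 patients per group, 1:1 (section 2.4); standardised effect d = 0.75, two-sided alpha 0.05, t test, power above 0.80 (section 2.3); two flows under the primary outcome (section 3.1); 0.05 for all tests (section 3.3).

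**Assumed.** The correlation r between the two test statistics is not given, so a range is shown. For joint power, d = 0.75 is assumed on both flows.

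**Step 1: the plan's own figure.** For a two-sample t test, the noncentrality is d × √(n/2) = 0.75 × √15 = 2.905 on 58 degrees of freedom, with critical value 2.002. The noncentral t distribution gives power 0.815 (normal approximation 0.828). The smallest sufficient n is 29 per group. The stated power above 0.80 is reproduced for one test at 0.05.

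**Step 2: either flow may count.** If the tests are independent, the chance of at least one false positive is 1 − (1 − 0.05)² = 1 − 0.9025 = 0.0975. With correlation r it is 1 − P(|Z1| < 1.96 and |Z2| < 1.96) from the bivariate normal distribution:

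| r (assumed) | Chance of at least one false positive |
|---|---|
| 0 | 9.75% |
| 0.3 | 9.5% |
| 0.5 | 9.1% |
| 0.7 | 8.4% |
| 0.9 | 7.0% |
| 1 | 5.0% |

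Simulated t tests with 30 per group agree: 9.8%, 9.5%, 9.0% and 8.3% at r = 0, 0.3, 0.5 and 0.7. Counting only false positives that favour photobiomodulation, the figures are 4.9% (r = 0) and 4.5% (r = 0.5), against 2.5% for one test.

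**Step 3: both flows required.** The error cannot exceed that of either single test, so it stays within 5%. Power is the chance that both tests are significant. If independent, this is 0.815² = 0.664. Simulated pairs of t tests with 30 per group and d = 0.75 on both flows give:

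| r (assumed) | Power, both significant at 0.05 |
|---|---|
| 0 | 0.66 |
| 0.5 | 0.71 |
| 0.7 | 0.73 |
| 0.9 | 0.77 |

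The ceiling, at r = 1, is 0.815.

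**Step 4: one flow named, the other tested second.** The first test uses the full 0.05 and has the power of step 1, 0.815. The second is tested at 0.05 only after the first is significant, so the chance of any false positive across the pair stays at or below 5%.

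**The case against.** The strongest objection is that the article never says that a result on either flow makes the trial positive. The sample size section speaks of one salivary volume and one test, which fits a single intended primary measure that was left unnamed. A full protocol or analysis plan, not shown here, may name it. This stands as far as the error rate goes. A reader might infer that the false positive rate is about 9% and not 5%. The document does not support that as a flat statement, because it requires both an either-flow rule and a correlation near 0.5, and the article states neither.

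A reader might also infer that splitting alpha between the flows would necessarily lose the planned power. For one given flow tested at 0.025, power at d = 0.75 does fall to 72.6%, and 36 per group would be needed for 80%. But if success on either flow counts, the chance of at least one significant result at 0.025 is about 0.93 at r = 0 and 0.83 at r = 0.7, with d = 0.75 on both flows. It drops below 0.80 only at higher correlation (about 0.79 at r = 0.9) or if the second flow responds much less. At d = 1.0, even single-flow power at 0.025 is 93.9%. The loss is conditional.

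Finally, it is tempting to nominate unstimulated flow because it is collected first. The document gives no basis for that preference, since it treats the two flows equally.

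What the objection does not remove is the ambiguity itself. What the primary outcome is belongs in section 3.1 and underlies the sample size. The article does define it, and the definition covers two variables.

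**Conclusion.** The point holds as an ambiguity in the primary outcome with conditional consequences. It is certain from the text that two flows stand under one primary heading, that the trial was sized for one test, and that no rule says which flow decides. The size depends on the rule:

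- Either flow counts: false positive chance up to 9.75%, about 8% to 10% for assumed correlations of 0 to 0.7, and above 5% for any correlation below 1.
- Both flows required: error within 5%, but power about 0.66 to 0.77 for assumed correlations of 0 to 0.9, with d = 0.75 on both flows, against the stated 0.80.
- One flow named in advance: 5% error and 81.5% power, as planned.

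Of these three, only the last keeps both the stated level and the stated power at d = 0.75 without relying on a very high correlation between the flows. The matter should be settled because it determines what counts as a positive trial.

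**What to change.** Before unblinding, name one flow in section 3.1 as the primary outcome. Which one is the investigators' choice. The sample size section should then refer to that flow. Add to section 3.3 that the other flow is tested at two-sided 0.05 only if the primary flow is significant, and is otherwise reported descriptively.

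This costs about one sentence in each place and no additional patients. The small downside is that a positive result on the second flow alone can no longer be claimed as confirmatory.
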